#### Primary endpoint analysis

2.6.1

The primary endpoint is the change in functional capacity from baseline to the end of the 8-week intervention, assessed by VO₂peak measured during cardiopulmonary exercise testing.

The primary efficacy analysis will compare VO₂peak at 8 weeks between the telerehabilitation group and the control group using analysis of covariance (ANCOVA), with treatment group as the fixed factor and baseline VO₂peak as the mandatory covariate. Additional pre-specified covariates may include age, sex, NYHA class, and baseline frailty level, if clinically relevant or imbalanced between groups at baseline. The treatment effect will be expressed as adjusted mean difference between groups, with 95% confidence interval and *p*-value.

As a supportive analysis, the absolute change in VO₂peak from baseline to 8 weeks will also be calculated and compared between groups. A longitudinal analysis will be performed using a linear mixed model for repeated measures, including time, group, and group-by-time interaction as fixed effects and participant as a random effect. This model will allow the evaluation of VO₂peak trajectories over time, including baseline, post-treatment, and follow-up assessments. The 24-week assessment will be used to evaluate the maintenance of treatment effects and will be interpreted as a follow-up analysis rather than as the primary confirmatory endpoint.

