### Outcomes

2.4

The outcome measures of the TeleRiab4FRA study were defined to provide a multidimensional evaluation of the effects of high-technology telerehabilitation in frail and pre-frail older adults with CHF. Outcomes include functional capacity, frailty status, physical performance, health-related quality of life, cognitive function, biochemical parameters, caregiver-related outcomes, technological usability, treatment adherence, and safety. All outcomes will be collected according to the pre-specified assessment schedule and in line with the registered trial protocol.

The primary outcome is the change in functional capacity from baseline to the end of the 8-week intervention, measured as VO₂peak during CPET (35, 36). The primary efficacy analysis will compare VO₂peak at 8 weeks between the telerehabilitation group and the control group, adjusted for baseline values. VO₂peak will also be assessed at the 24-week follow-up to evaluate the maintenance of treatment effects over time (37).

The key secondary outcome is the change in frailty status assessed using the IFI (26), which will be collected at baseline, 4 weeks, 8 weeks, 16 weeks, and 24 weeks, and changes over time will be compared between the telerehabilitation and control groups.

Physical performance will be assessed using the SPPB, which includes balance, gait speed, and chair stand tests (38, 39). The SPPB provides a composite score ranging from 0 to 12, with higher scores indicating better lower-extremity function and physical performance. SPPB will be assessed at baseline, 4 weeks, 8 weeks, 16 weeks, and 24 weeks.

Health-related quality of life will be evaluated using the Short Form-36 Health Survey (SF-36), which assesses multiple domains, including physical functioning, role limitations, bodily pain, general health, vitality, social functioning, emotional well-being, and mental health (40, 41). Scores range from 0 to 100, with higher scores indicating better perceived health status and quality of life. SF-36 will be administered at baseline, 8 weeks, and 24 weeks.

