### Statistical analysis

2.6

All statistical analyses will be performed according to a pre-specified Statistical Analysis Plan before database lock. Descriptive statistics will be used to summarize baseline demographic, clinical, functional, cognitive, biochemical, and caregiver-related characteristics. Continuous variables will be reported as mean and standard deviation or median and interquartile range, according to data distribution. Categorical variables will be summarized as absolute frequencies and percentages. Normality will be assessed using graphical methods and appropriate statistical tests.

The primary analysis will be conducted according to the intention-to-treat (ITT) principle, including all randomized participants and analyzing them according to their original allocation group. A per-protocol (PP) analysis will also be performed as a sensitivity analysis, including participants who complete at least 80% of the scheduled motor and cognitive training sessions without major protocol deviations. The safety population will include all participants who start the assigned rehabilitation program and will be used for the description of adverse events and safety-related outcomes.

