#### Secondary endpoint analysis

2.6.2

Secondary outcomes will be analyzed according to their measurement scale and distribution. Continuous outcomes, including IFI, SPPB, SF-36, MMSE, MoCA, BNP, ANP, ZBI-12, and PSS-10 scores, will be summarized at each timepoint and analyzed using ANCOVA models adjusted for the corresponding baseline value when post-treatment comparisons between groups are performed.

When repeated measurements are available across multiple timepoints, linear mixed models will be used to assess changes over time and group-by-time interactions. These models will include all available observations and will allow the evaluation of outcome trajectories across baseline, 4 weeks, 8 weeks, 16 weeks, and 24 weeks, when applicable.

The Italian Frailty Index will be considered the key secondary endpoint. Other clinically relevant secondary outcomes will include SPPB, SF-36, and treatment adherence. For this pre-defined set of clinically relevant secondary outcomes, adjustment for multiple comparisons will be performed using the Holm-Bonferroni procedure, with an overall significance level of 0.05. All other secondary and exploratory outcomes, including cognitive measures, biochemical parameters, caregiver-related measures, and technological usability, will be interpreted primarily in a descriptive and exploratory manner, with estimates of effect, 95% confidence intervals, and *p*-values reported where appropriate.

Treatment adherence will be calculated as the percentage of scheduled motor and cognitive sessions completed during the 8-week intervention period. Between-group differences in adherence will be analyzed descriptively and, where appropriate, using parametric or non-parametric tests according to data distribution. Usability, assessed using the System Usability Scale in the telerehabilitation group only, will be reported descriptively as mean, standard deviation, median, interquartile range, and score distribution.

Safety outcomes, including adverse events, symptoms during exercise, abnormal clinical parameters, technical issues, session interruptions, and protocol deviations, will be summarized by group using frequencies, percentages, and event rates where appropriate.

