#### Sample size calculation

2.6.3

The sample size was calculated on the basis of the primary endpoint, defined as the change in functional capacity measured by VO₂peak during cardiopulmonary exercise testing from baseline to the end of the 8-week intervention.

A between-group difference of 2.5 mL/kg/min in VO₂peak (50) was considered clinically meaningful. Assuming a standard deviation of 3.5 mL/kg/min, corresponding to a Cohen's d effect size of approximately 0.71, the sample size calculation was performed using G*Power software, based on a two-tailed test for the difference between two independent means, with a significance level of *α* = 0.05, statistical power of 80%, and 1:1 allocation.

The calculation indicated that 33 participants per group, corresponding to 66 participants overall, are required to detect the expected difference in the primary endpoint. Considering an anticipated dropout rate of approximately 15%–20%, the study plans to enroll approximately 80 participants overall, in order to preserve adequate statistical power for the primary efficacy analysis.

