#### Handling of missing data and dropouts

2.6.4

Missing data will be described by treatment group, outcome, and assessment timepoint. The amount, pattern, and potential reasons for missingness will be examined to evaluate whether missing data are likely to be missing completely at random, missing at random, or not missing at random.

The primary analysis will be conducted on the ITT population. Linear mixed models for repeated measures will be used as part of the analytical strategy because they allow inclusion of participants with partially observed follow-up data under the missing at random assumption. If the proportion of missing data at the primary post-treatment assessment is relevant or unbalanced between groups, sensitivity analyses using multiple imputation will be performed. The imputation model may include treatment group, baseline value of the outcome, age, sex, NYHA class, frailty level, and other variables associated with missingness or outcome values.

Dropouts and protocol deviations will be documented in the CRF, including the timing and reason for withdrawal whenever available. Participants who discontinue the intervention but remain available for outcome assessment will be invited to complete follow-up evaluations according to the original study schedule. Per-protocol analyses will be conducted as sensitivity analyses to assess the robustness of the primary findings among participants with adequate intervention exposure and without major protocol deviations.

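### The longitudinal VO₂peak model, read as written, fixes one correlation across weeks 0, 8 and 24 and leaves baseline unadjusted, so its week-24 interval may be too narrow

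*Protocol article*

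**What the plan says.** Section 2.6.1 gives VO₂peak two analyses. The primary one compares week-8 values "using analysis of covariance (ANCOVA), with treatment group as the fixed factor and baseline VO₂peak as the mandatory covariate". The longitudinal one is a "linear mixed model for repeated measures, including time, group, and group-by-time interaction as fixed effects and participant as a random effect"; the same paragraph says that it covers baseline, post-treatment and follow-up. No residual covariance is stated. The 24-week result is to be "interpreted as a follow-up analysis rather than as the primary confirmatory endpoint".

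Table 4 places VO₂peak at baseline, week 8 and week 24, and section 2.4 gives the last visit its purpose: "VO₂peak will also be assessed at the 24-week follow-up to evaluate the maintenance of treatment effects over time".

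Section 2.6.2 says that for repeatedly measured secondary outcomes "linear mixed models will be used to assess changes over time and group-by-time interactions", without naming a random effect or a covariance structure. It also provides ANCOVA adjusted for the baseline value for post-treatment group comparisons. Section 2.6.4 adds that "Linear mixed models for repeated measures will be used as part of the analytical strategy", relying on missing at random. Section 2.6 refers to a separate plan, which is not shown: "All statistical analyses will be performed according to a pre-specified Statistical Analysis Plan before database lock".

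**The concern.** A participant random effect with independent residuals implies compound symmetry: one variance at every visit, and the same correlation for tests 8, 16 and 24 weeks apart. The schedule makes that doubtful. Eight weeks of prescribed training are followed by sixteen weeks without study sessions, during which outside rehabilitation is allowed and recorded. If tests further apart are less alike, the model averages over unequal contrast variances. It then overstates the variance of the short-interval change and understates that of the long-interval change.

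Because baseline is an outcome and the group effect is free at every visit, the group-by-time contrasts are plain differences in change. The baseline adjustment that the same section makes mandatory for the ANCOVA is lost in this model.

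At stake is the precision claimed for the week-24 VO₂peak result, for which section 2.6.1 names no other model.

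**Working it through.** **The plan's own figure.** Section 2.6.3 uses "A between-group difference of 2.5 mL/kg/min in VO₂peak", an SD of 3.5, two-sided α of 0.05, 80% power and 1:1 allocation. A two-sample t-test with the noncentral t distribution at d = 0.71 gives power 0.798 with 32 per arm and 0.811 with 33. The stated 33 per arm is reproduced, and nothing below changes it.

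**Inputs.** n = 33 per arm (section 2.6.3). VO₂peak visits at weeks 0, 8 and 24 (Table 4). SD σ = 3.5 taken at each visit; with equal SDs it scales the standard errors but not their ratios. Correlations between visits are not in the documents and are assumed. Data are taken as complete.

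**Formulas.** Let r̄ be the mean of the three pairwise correlations.

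- Random-intercept residual variance: σ²(1 − r̄)
- Model SE of the between-group difference in change: σ√[4(1 − r̄)/n]
- True SE for visits s and t: σ√[4(1 − r_st)/n]
- Ratio k = model SE / true SE = √[(1 − r̄)/(1 − r_st)]
- True error of a nominal 5% test: 2[1 − Φ(1.96k)]

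**Worked case**, r(0,8)/r(0,24)/r(8,24) = 0.80/0.60/0.70, so r̄ = 0.70:

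- Model SE = 3.5 × √(4 × 0.30/33) = 0.667
- True SE at week 8 = 3.5 × √(4 × 0.20/33) = 0.545, so k = 1.22
- True SE at week 24 = 3.5 × √(4 × 0.40/33) = 0.771, so k = 0.87

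**Range.** The last two rows are pure serial correlation of 0.85 and 0.95 per 8 weeks.

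| r(0,8)/r(0,24)/r(8,24) | k, 0→8 | k, 0→24 | error 0→8 | error 0→24 | error 8→24 |
|---|---|---|---|---|---|
| 0.70/0.70/0.70 | 1.00 | 1.00 | 5.0% | 5.0% | 5.0% |
| 0.75/0.65/0.70 | 1.10 | 0.93 | 3.2% | 7.0% | 5.0% |
| 0.80/0.60/0.70 | 1.22 | 0.87 | 1.6% | 9.0% | 5.0% |
| 0.85/0.55/0.65 | 1.45 | 0.84 | 0.4% | 10.0% | 6.2% |
| 0.85/0.614/0.7225 | 1.34 | 0.84 | 0.8% | 10.0% | 5.3% |
| 0.95/0.857/0.9025 | 1.39 | 0.82 | 0.6% | 10.7% | 5.1% |

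**Shape of the correlation.** Take r = a + (1 − a − e)ρ^m, with m the number of 8-week steps, ρ from 0.85 to 0.95, a the stable between-person share of variance and e the measurement-noise share.

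- e = 10–15%, a = 0: error at week 24 is 7.0–8.6%.
- e = 10–15%, a = 50–60%: error at week 24 is 5.8–7.6%.
- e = 0, any a: the three-visit ratios do not move, because every 1 − r shrinks by the same factor.

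**Unequal SDs.** With equal correlation 0.70 and SDs 3.5/3.5/4.5, k is 1.13 at week 8 and 0.95 at week 24; the week-24 error is 6.3%.

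**Simulation.** In 10,000 null trials per scenario, the week-24 error was 5.0% for the first row of the table, 7.3%, 9.4% and 9.9% for the next three, and 6.5% for the unequal-SD case. The planned week-8 ANCOVA stayed at 4.8–5.2% throughout.

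**Baseline adjustment.** With equal SDs, the SE of an adjusted comparison divided by that of a change score is √[(1 + r)/2]. At r(0,24) = 0.857 this is 0.964 and at 0.614 it is 0.898. Adjustment would therefore cut the true week-24 SE by about 4% to 10% in the serial-correlation cases.

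**The case against.** The strongest reply is that the text lists what the model includes and does not rule out a residual covariance structure. That detail is often left to an analysis plan, and one exists that is not shown. This stands as a limit: the unseen plan may already state a richer structure. It does not dispose of the point, because the one covariance feature that the article states is the restrictive one, and a plan that follows it would inherit the restriction.

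The size is also open to challenge. Pure serial correlation assumes no measurement noise, and it gives the top of the range. With noise and a stable person component the week-24 error is nearer 6–8%, and with constant variance and correlation nothing is wrong. This stands, and the range reflects it.

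Three stronger readings are tempting, and the documents support none of them.

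- A reader might infer that the primary result is at risk. It is not: that analysis is a separate ANCOVA. At week 8 only the longitudinal contrast is affected, and in the cases examined it errs on the conservative side.
- A reader might infer that the five-visit outcomes, including the key secondary Italian Frailty Index, suffer a still larger error. Section 2.6.2 names no random effect for those models and offers baseline-adjusted ANCOVA for group comparisons, so no error rate can be attributed to them.
- A reader might infer that maintenance is certain to be tested anti-conservatively. The article does not define the maintenance contrast. If it is change from week 8 to week 24, the error is 5.0–6.2% in the tabulated cases.

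**Conclusion.** The point holds in a limited, conditional form. The longitudinal VO₂peak model as written implies compound symmetry and unadjusted change-score contrasts. If correlation falls with time, its interval for change from baseline is too wide at week 8 and too narrow at week 24. The week-24 error is then roughly 6–11% against a nominal 5%, depending on the assumed correlation shape.

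This rests on complete data, 33 per arm and correlations that the documents do not supply. The effect of 15–20% dropout was not quantified.

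The consequence is confined to a follow-up analysis. The sample size is unaffected. The change is still worth making, because a better specification is available at almost no cost.

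**What to change.** In section 2.6.1, replace the participant random effect with:

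- visit as a categorical factor;
- unstructured within-participant covariance, with heterogeneous Toeplitz as the named fallback if the model does not converge;
- Kenward-Roger degrees of freedom;
- baseline means constrained equal across arms, or baseline and baseline-by-visit as covariates.

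Report the between-group difference at week 8 and at week 24 from this model. Apply the same specification to the mixed models in sections 2.6.2 and 2.6.4, which at present state no covariance structure.

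The cost is wording plus a few parameters: 3 × 4/2 = 6 covariance parameters for VO₂peak, or 5 × 6/2 = 15 for five-visit outcomes, instead of 2. Both are feasible with about 80 patients. If correlation really is constant, little is lost.

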#### Secondary endpoint analysis

2.6.2

Secondary outcomes will be analyzed according to their measurement scale and distribution. Continuous outcomes, including IFI, SPPB, SF-36, MMSE, MoCA, BNP, ANP, ZBI-12, and PSS-10 scores, will be summarized at each timepoint and analyzed using ANCOVA models adjusted for the corresponding baseline value when post-treatment comparisons between groups are performed.

When repeated measurements are available across multiple timepoints, linear mixed models will be used to assess changes over time and group-by-time interactions. These models will include all available observations and will allow the evaluation of outcome trajectories across baseline, 4 weeks, 8 weeks, 16 weeks, and 24 weeks, when applicable.

The Italian Frailty Index will be considered the key secondary endpoint. Other clinically relevant secondary outcomes will include SPPB, SF-36, and treatment adherence. For this pre-defined set of clinically relevant secondary outcomes, adjustment for multiple comparisons will be performed using the Holm-Bonferroni procedure, with an overall significance level of 0.05. All other secondary and exploratory outcomes, including cognitive measures, biochemical parameters, caregiver-related measures, and technological usability, will be interpreted primarily in a descriptive and exploratory manner, with estimates of effect, 95% confidence intervals, and *p*-values reported where appropriate.

Treatment adherence will be calculated as the percentage of scheduled motor and cognitive sessions completed during the 8-week intervention period. Between-group differences in adherence will be analyzed descriptively and, where appropriate, using parametric or non-parametric tests according to data distribution. Usability, assessed using the System Usability Scale in the telerehabilitation group only, will be reported descriptively as mean, standard deviation, median, interquartile range, and score distribution.

Safety outcomes, including adverse events, symptoms during exercise, abnormal clinical parameters, technical issues, session interruptions, and protocol deviations, will be summarized by group using frequencies, percentages, and event rates where appropriate.

Predefined exploratory subgroup analyses will examine whether treatment effects vary according to baseline frailty status (pre-frail versus frail, and where appropriate moderate versus severe frailty), NYHA functional class (I–II versus III), sex, and age (for example, ≤80 versus >80 years). Treatment-by-subgroup interaction terms may be estimated within the relevant ANCOVA or mixed-effects models. Because the trial is not powered for subgroup effects, these analyses will be considered hypothesis-generating and interpreted cautiously using interaction estimates and 95% confidence intervals.

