#### Control group

2.2.2

Participants allocated to the control group will receive an individualized home-based rehabilitation program supervised by a caregiver or family member. The program will be initially explained in person by the rehabilitation team and will include motor and cognitive exercises matched to the patient's frailty profile and comparable in content and duration to those prescribed for the telerehabilitation group.

The motor component will last approximately 60 min per session, including warm-up, active exercise, and cool-down. The cognitive component will last approximately 30 min per session and will include exercises targeting the same cognitive domains addressed in the telerehabilitation group. Treatment frequency will follow the same frailty-based schedule used for the telerehabilitation group: 2–4 sessions per week during the first 4 weeks and 3–5 sessions per week from week 5 to week 8 for pre-frail patients, and 3–5 sessions per week throughout the 8-week program for frail patients.

Caregivers will receive standardized in-person training on the prescribed exercises, session schedule, safe assistance, recognition of warning symptoms, measurement of basic clinical parameters when required, and procedures for contacting the clinical team. Before home treatment begins, caregiver understanding and practical competence will be verified using a structured checklist. Participants and caregivers will receive a written exercise schedule and illustrated instructions and will complete a daily activity diary documenting exercises performed, session duration, perceived exertion and tolerance, symptoms, adverse events, and any deviations from the prescribed program. A member of the rehabilitation team will conduct a structured weekly telephone or video contact to review the diary, verify completion and quality of the sessions, reinforce correct exercise execution, resolve doubts, and document protocol deviations. Diaries will be reviewed at weeks 4 and 8, and fidelity will be summarized as the proportion of prescribed sessions completed and the proportion performed according to the planned duration and exercise content.

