Exercise personalization	Tailored according to clinical status, frailty level, baseline functional capacity, and exercise tolerance	Tailored according to clinical status, frailty level, baseline functional capacity, and exercise tolerance
Frequency in pre-frail patients	2–4 sessions/week during weeks 1–4; 3–5 sessions/week during weeks 5–8	2–4 sessions/week during weeks 1–4; 3–5 sessions/week during weeks 5–8
Frequency in frail patients	3–5 sessions/week throughout the 8-week program	3–5 sessions/week throughout the 8-week program
Monitoring	Remote monitoring of ECG, heart rate, peripheral oxygen saturation, and blood pressure	Measurement of basic clinical parameters when required
Technology	CE-marked digital telerehabilitation platform with connected devices and remote monitoring tools	No digital telerehabilitation platform; use of diary and caregiver support
Adherence assessment	Platform-based monitoring and session attendance	Daily activity diary and reported session completion
Safety procedures	Real-time supervision, remote monitoring, session interruption in case of warning signs or abnormal parameters	Caregiver instruction, symptom monitoring, interruption of exercise in case of warning signs
Caregiver role	Support in device use and home setting, when needed	Direct supervision of home-based sessions
Main difference between groups	Digital synchronous delivery with remote professional supervision and monitoring	Conventional home-based delivery supervised by caregiver/family member

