The VRRS Home Kit includes inertial sensors for movement tracking, wearable sensors for heart rate and peripheral oxygen saturation, a spirometer for guided respiratory exercises, and a health monitor for blood pressure and single-lead electrocardiographic data. Movement sensors provide information on exercise execution and task completion, whereas physiological devices support safety surveillance and evaluation of exercise response. Data are reviewed in real time during synchronous sessions when technically available; session records and stored measurements can also be reviewed after the session. The platform does not autonomously diagnose clinical deterioration: all alerts, abnormal values, or performance concerns are interpreted by qualified healthcare professionals according to the study safety procedures.

Personalization is clinician-driven and follows prespecified clinical rules. At baseline, the rehabilitation team selects the motor and cognitive modules, session frequency, task complexity, exercise intensity, and progression targets according to CPET results, NYHA class, frailty profile, SPPB performance, cognitive status, comorbidities, and exercise tolerance. During the intervention, the clinician may progress, maintain, simplify, or interrupt an activity on the basis of observed execution, Borg-rated exertion, symptoms, vital-sign response, completion rate, and changes in functional status. Modifications are documented in the treatment record. Thus, the platform functions as a delivery, monitoring, and decision-support environment, while responsibility for personalization remains with the rehabilitation professional.

To improve usability in older frail and pre-frail patients, the technological pathway includes structured patient and caregiver education, simplified instructions for device use, and remote technical support when required. In case of technical issues, poor connectivity, difficulty in using the devices, abnormal clinical parameters, or symptoms suggestive of clinical instability, the session can be interrupted and the patient can be contacted for further assessment. If needed, the patient may be referred for in-person clinical evaluation to ensure safety and continuity of care.

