### Safety management and contingency planning

2.5

A structured safety management and contingency plan will be implemented to minimize clinical and operational risks during the TeleRiab4FRA study. The safety procedures will apply to both study groups, with specific measures adapted to the mode of delivery of each intervention.

In the telerehabilitation group, all sessions will be delivered synchronously and remotely supervised by qualified healthcare professionals. During each session, the rehabilitation team will monitor the patient's clinical status, exercise execution, and physiological response to training. The telerehabilitation platform will support remote monitoring of relevant clinical parameters, including heart rate, peripheral oxygen saturation, blood pressure, and single-lead electrocardiographic data. These data will be used to guide exercise progression, verify tolerance, and identify potential warning signs.

Before starting the home-based program, patients and caregivers will receive in-person training on the use of the telerehabilitation devices, correct sensor placement, recognition of warning symptoms, and procedures to follow in case of clinical or technical problems. Patients will be instructed to stop exercise and immediately inform the rehabilitation team in case of chest pain, marked dyspnea, dizziness, palpitations, excessive fatigue, neurological symptoms, altered consciousness, falls, or any other concerning symptom.

The rehabilitation session will be interrupted in the presence of abnormal clinical parameters, relevant symptoms, unsafe exercise execution, or technical issues that prevent adequate supervision. In such cases, the patient will be contacted by the rehabilitation team and, when necessary, referred for cardiological evaluation, in-person rehabilitation assessment, or emergency medical care according to local clinical procedures.

In the control group, patients will perform the home-based program under the supervision of a caregiver or family member. Caregivers will receive specific instructions on how to support the patient during the sessions, recognize signs of intolerance, measure basic clinical parameters when required, interrupt exercise in case of warning symptoms, and contact the clinical team if clinical concerns arise. The daily activity diary will also be used to record session completion, perceived tolerance, symptoms, and any adverse events.

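### By-group rates of events found during sessions mix detection with risk, because the two arms are watched differently by design; keep them apart from events ascertained the same way in both arms

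*Protocol article*

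**What the plan says.** Section 2.6.2 lists the safety items together: "Safety outcomes, including adverse events, symptoms during exercise, abnormal clinical parameters, technical issues, session interruptions, and protocol deviations, will be summarized by group". The sentence ends by saying that they "will be summarized by group using frequencies, percentages, and event rates where appropriate". Section 2.6 assigns this description to everyone who starts the allocated programme.

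The means of finding events differ by arm:

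- **Telerehabilitation.** Section 2.5: "During each session, the rehabilitation team will monitor the patient's clinical status, exercise execution, and physiological response to training". Table 2 lists the signals: "Remote monitoring of ECG, heart rate, peripheral oxygen saturation, and blood pressure". Section 2.3 adds a qualifier: "Data are reviewed in real time during synchronous sessions when technically available".
- **Control.** Sessions are supervised by a caregiver or family member. Table 2 gives the monitoring as "Measurement of basic clinical parameters when required". Section 2.5: "The daily activity diary will also be used to record session completion, perceived tolerance, symptoms, and any adverse events". Section 2.2.2: "A member of the rehabilitation team will conduct a structured weekly telephone or video contact to review the diary".

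Table 4 schedules adverse events for both arms at 4, 8, 16 and 24 weeks. The abstract (Expected results) includes safety among the outcomes on which favourable effects are hypothesised. Section 3 expects the platform to help in spotting symptoms, abnormal parameters and technical problems early. The limitations (section 5) mention the lack of blinding for subjective outcomes but not unequal safety ascertainment.

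**The concern.** A recorded event rate is the true rate multiplied by the chance that an event is noticed and written down. If that chance differs between arms, the recorded rates can differ when the true rates do not, or agree when the true rates differ. Here the chance differs by design for anything that happens during a session, and the article itself expects the platform to reveal more.

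The article also hypothesises a favourable safety effect. A platform that finds more raises the recorded counts of its own arm, so the table could run against the hypothesis even if it were true. Section 2.6.2 does not separate events found through session monitoring from events collected the same way in both arms. A reader of the final table would have no means of telling them apart.

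**Working it through.** The document gives no figure for safety events or detection, so there is none to reproduce. The sample size in section 2.6.3 concerns peak oxygen uptake and has no bearing here. The check is a comparison of passages followed by an illustration.

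**1. Items in section 2.6.2, by how each arm finds them**

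| Item | Telerehabilitation | Control | Comparable? |
|---|---|---|---|
| Abnormal parameters | Signals monitored by professionals in each session, live when technically available | Measured when required | No |
| Symptoms during exercise | Seen or reported live to a professional | Noted by patient or caregiver in the diary, reviewed weekly | No |
| Session interruptions | Symptoms, abnormal values, unsafe execution, or technical failure that prevents supervision | Warning signs noticed by patient or caregiver | No; the reasons differ |
| Technical issues | Can occur | No platform, so platform faults cannot occur | No control counterpart |
| Adverse events at weeks 4, 8, 16 and 24 | Scheduled visit | Scheduled visit | Yes, if asked in the same way |
| Serious adverse events | Reported under common procedures | Reported under common procedures | Largely |
| Events in weeks 9–24 | No study sessions | No study sessions | Little affected by session monitoring |

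**2. Number of sessions in 8 weeks (section 2.2.1; same schedule in control)**

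- Pre-frail: 4×2 + 4×3 = 20 up to 4×4 + 4×5 = 36.
- Frail: 8×3 = 24 up to 8×5 = 40.

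Both arms are thus scheduled for 20 to 40 sessions. What differs is who watches and with what.

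**3. Effect of unequal detection under equal true risk**

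Assumptions, none of them from the document: per-session event probability *p*, equal in both arms; *m* = 30 sessions (the middle of 20 to 40); detection *s* = 0.95 in telerehabilitation and 0.8 down to 0.2 in control.

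P(at least one recorded event) = 1 − (1 − *p*·*s*)^*m*

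For *p* = 0.02, telerehabilitation: 1 − (1 − 0.019)^30 = 43.8%.

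| Control detection | Control, recorded | Apparent risk ratio | Apparent rate ratio (0.95/*s*) |
|---|---|---|---|
| 0.8 | 38.4% | 1.14 | 1.19 |
| 0.6 | 30.4% | 1.44 | 1.58 |
| 0.4 | 21.4% | 2.04 | 2.38 |
| 0.2 | 11.3% | 3.86 | 4.75 |

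Over *p* = 0.01 to 0.05, the apparent risk ratio runs from 1.09 (*p* = 0.05, control detection 0.8) to 4.27 (*p* = 0.01, control detection 0.2). The true ratio is 1 throughout.

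**4. Direction outside sessions**

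The daily diary and the structured weekly contact are described only for control. For events between sessions, control may therefore be the better-observed arm. If detection were 0.6 in telerehabilitation and 0.95 in control, the apparent rate ratio would be 0.6/0.95 = 0.63. The two mechanisms pull in opposite directions, and the document gives nothing with which to weigh them.

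**The case against.** The best defence is that nothing confirmatory is planned. Section 2.6.2 describes safety by group without a test, interval or decision rule. The last paragraph of section 1 places safety among the outcomes to be read as secondary or exploratory. By-group description of harms is standard, and the items are listed separately, not merged into a composite. All of this stands: the table itself is not the fault. What remains is that the abstract hypothesises a favourable safety effect, and the plan does not say which rows can speak to it.

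The control arm is also better observed than a quick reading suggests. Caregivers are trained, their competence is checked, parameters are measured when required, a professional calls weekly, and adverse events are collected at the same four visits as in telerehabilitation. This narrows the problem to session-detected events but does not remove it, since the weekly contact largely works from the diary.

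A reader might infer more than the document supports:

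- *That group rates show detection and not risk.* They mix the two. Serious events, events found at common visits and events in weeks 9–24 depend little on session monitoring.
- *That telerehabilitation will look less safe overall.* This is plausible for events during sessions only. The control-only diary and weekly contact leave the overall direction open.
- *That 20 to 40 supervised sessions against 8 weekly contacts (20/8 = 2.5 to 40/8 = 5) measures the detection gap.* It counts professional contacts. Control has the same scheduled sessions, watched by a caregiver.

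Layout of tables and wording of questions may sit in the analysis plan or case report form, which are not shown. The point therefore rests on what the article does state: one by-group list and a comparative safety hypothesis.

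**Conclusion.** The point holds as a cheap improvement, not as an error in descriptive safety reporting. By-group rates of abnormal parameters, exercise symptoms and session interruptions mix detection with risk. They cannot test the hypothesised favourable safety effect, and technical issues have no control counterpart at all. Unequal detection alone could produce apparent risk ratios of about 1.1 to 4.3 for session-detected events, but only on the assumed values: equal true risk, 30 sessions, detection of 0.95 against 0.8 to 0.2, and *p* of 0.01 to 0.05. The actual size and the overall direction cannot be derived from the document. The conclusion rests on the stated difference in monitoring, not on the illustration.

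**What to change.** 1. Base any between-group safety statement on events ascertained alike in both arms: deaths, hospitalisations, serious adverse events, and adverse events elicited with one identical question set at the week 4, 8, 16 and 24 visits already in Table 4.
2. Report platform-detected abnormal parameters and technical issues separately for telerehabilitation, per session delivered, without a between-group contrast.
3. Keep exercise symptoms and session interruptions for both arms, split by reason and source and labelled as not comparable between groups. Showing interruptions for telerehabilitation only would discard control data that the protocol has recorded.
4. Add unequal ascertainment of safety events to the limitations in section 5.

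The cost is wording in the analysis plan and a short standard question set at visits already scheduled. Sample size, treatment and visit schedule do not change. The downside is that fewer event types support a between-group statement, and with about 80 participants that statement remains descriptive.
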